### Sample size calculation and statistical analysis

According to the findings of a previously published epidemiological study [17] that the proportion of adults with an apnea/hypopnoea index (AHI) ≥ 15 corresponds to 16.9% of the Brazilian population and that of a previous study [18] that AHI ≥ 15 had an approximately 50% prevalence rate in patients with CKD undergoing conventional dialysis (3 times a week, 4 h per session) [19], the sample size was calculated as 57 patients, with an *α* = 0.05 and *β* = 90% (test power).

The Kolmogorov–Smirnov normality test will first be performed to determine whether a normal distribution sample is present. A descriptive analysis will be performed, with the data expressed as either mean and standard deviation or median values and 95% confidence intervals, as appropriate. One-way analysis of variance will be used for comparisons between work shifts once the samples have a normal distribution. V_0.2_ and ΔV (%) values will be linearly correlated with the AHI, for which either the Pearson or Spearman correlation test will be used, depending on the sample distribution. Either the non-paired Student *t* test or Mann–Whitney test will be used for comparisons between individuals with and those without OSA.

In addition, a logistic regression analysis of continuous factors with categorical responses will be performed. Receiver operating characteristic (ROC) curves will be constructed to determine the sensitivity (true-positive rate) versus 100% specificity (false-positive rate) at various levels of the measured $\Delta \dot{V}$ (%) and V_0.2_ (%) to identify the cut-off value yielding the largest number of correctly classified patients. The statistical analysis will be performed by an experienced statistician using the JMP version 8.0 (SAS/STAT® Software, SAS Institute Inc., Cary, NC, USA) and SPSS version 16.0 programs (Somers NY). A 5% level of significance and 95% confidence interval will be applied.

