### Randomization

After the initial assessment and compliance with eligibility criteria, participants will be randomized into two intervention group [patients achieving diurnal hemodialysis and nocturnal hemodialysis] and the control group [CKD not submitted to dialysis]. Randomization numbers will be generated using a randomization table at a central office. A series of numbered, sealed, opaque envelopes will be used to ensure confidentiality. Each envelope will contain a card stipulating to which group the subject will be allocated.All patients underwent randomization protocol that will meet the eligibility criteria and be clinically stable.

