### Evaluation protocol

#### Clinical evaluation

Patients with chronic kidney diseases and end-stage renal disease undergoing dialysis, based on recommended procedures, will be submitted to general physical measurements performed by a well-trained physician and physical therapist before and after the dialysis session using precise instruments. The measurement protocol will include body weight (kg); height (cm); body mass index (BMI) calculated using the formula weight/height^2^[16]; circumferences (cm) of the neck, waist, and hip [20]; heart and respiratory rates; blood pressures; Mallampati index [21]; tonsil index [22]; heart rate variability [23]; maximum ventilatory pressure; negative expiratory pressure (NEP) test; and polysomnography (PSG; sleep study), as well as the administration of specific questionnaires addressing sleep apnea, excessive daytime sleepiness [24,25], symptoms of stress [12], and depression [12-14], anxiety [15], and quality of life [26,27].

The following data will be obtained from medical charts: biochemical values, associated pathological conditions, laboratory values (iron, intact-parathyroid hormone, haemoglobin, calcium, phosphorus, and creatinine), duration of dialysis therapy, comorbidities, and aetiology of kidney disease.

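### The only stated comparison between the dialysis groups is an unadjusted one-way ANOVA, although sex, age and BMI are collected; adjusting for them would add precision to the extent that they predict the outcome

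*Protocol article*

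**What the plan says.** The analysis paragraph of the protocol article (Sample size calculation and statistical analysis) gives one method for comparing the groups: "One-way analysis of variance will be used for comparisons between work shifts once the samples have a normal distribution". The article does not define work shifts. The Discussion speaks of different haemodialysis shifts, so dialysis shifts is the natural reading.

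The other methods in that section serve other questions. The t test or Mann–Whitney test compares patients with and without sleep apnoea. The correlations and ROC curves relate the negative-expiratory-pressure measures to apnoea. The remaining model is described only as "a logistic regression analysis of continuous factors with categorical responses will be performed", with neither the randomised group nor an adjustment set named.

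The candidate covariates are at hand. Eligibility (Subjects) admits both sexes and ages 18 to 80. Clinical evaluation lists BMI: "The measurement protocol will include body weight (kg); height (cm); body mass index (BMI". The Blinding section places baseline data collection before randomisation. On allocation, the Randomization section says "Randomization numbers will be generated using a randomization table at a central office" and describes sealed envelopes, with no stratum.

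**The concern.** A one-way ANOVA has group as its only term. Outcome variation due to sex, age or body size therefore stays in the residual and widens the interval for the day-versus-night difference. The article itself treats such variables as prognostic. Its Background gives sleep apnoea in 24.8% of men and 9.6% of women in São Paulo, and its sleep-apnoea risk questionnaire counts a BMI of 30 kg/m² or more as a positive item.

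If 57 is the total, there are 57/3 = 19 patients per group. Groups of that size will often differ by chance in these characteristics, and neither the allocation nor the analysis takes account of it. At stake is precision in a small trial, from variables that are collected anyway.

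**Working it through.** **Inputs from the article.** "the sample size was calculated as 57 patients"; three groups (day, night, not on dialysis); "A 5% level of significance and 95% confidence interval will be applied".

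**Assumptions.** 57 is the total, split 1:1:1 (the article gives neither point); two-sided test; true day–night difference 0.8 SD; R² of sex, age and BMI with a continuous outcome between 0 and 35%. The article gives neither an effect size nor an R².

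**The plan's own figure.** 57 rests on a binary outcome, AHI ≥ 15, which "corresponds to 16.9% of the Brazilian population" and "had an approximately 50% prevalence rate in patients with CKD undergoing conventional dialysis". At two-sided 5% and 90% power, the pooled formula for two proportions gives 41 per group, so 57 is not reproduced as a total. With 19 per group, power for 16.9% versus 50% is about 59%. That is a separate matter. Here it shows only that there may be little power to spare.

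**Step 1, gain before costs.** The relative sample size is 1/(1 − R²). At 15%, 25% and 35% this is 1/0.85 = 1.18, 1/0.75 = 1.33 and 1/0.65 = 1.54.

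**Step 2, cost of estimating three covariates.** With N = 57, g = 3 groups and q = 3 covariates, the expected variance rises by 1 + q/(N − g − q − 1) = 1 + 3/50 = 1.06. The net gain is 1/[(1 − R²) × 1.06] − 1.

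**Step 3, day-versus-night power.** Unadjusted, the noncentrality is 0.8/√(2/19) = 2.466 on 57 − 3 = 54 df, giving 67.8%. Adjusted, it is 2.466/√[(1 − R²) × 1.06] on 57 − 3 − 3 = 51 df.

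| R² | Net gain in patients | Noncentrality | Power |
|---|---|---|---|
| Unadjusted | – | 2.466 | 67.8% |
| 0% | −6% | 2.395 | 65.2% |
| 5% | −1% | 2.457 | 67.4% |
| 10% | 5% | 2.525 | 69.7% |
| 15% | 11% | 2.598 | 72.2% |
| 25% | 26% | 2.765 | 77.4% |
| 35% | 45% | 2.971 | 83.0% |

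The worst case is 67.8 − 65.2 = 2.6 points lost.

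**Step 4, sensitivity to the layout.** If only the two dialysis groups enter the model (N = 38), the cost factor is 1 + 3/32 = 1.094, and the gains at 15%, 25% and 35% are 8%, 22% and 41%. If 57 is per group (N = 171), the factor is 1 + 3/164 = 1.018, and they are about 15%, 31% and 51%.

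**Step 5, what sex alone could explain.** Take the Background prevalences with an assumed 60% men. Overall prevalence is 0.6 × 0.248 + 0.4 × 0.096 = 0.187. Sex then explains 0.6 × 0.4 × 0.152² / (0.187 × 0.813) = 3.6% of the variance in apnoea status (4.1% with equal numbers of each sex). The larger R² values would have to come mainly from age and BMI.

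**Step 6, chance imbalance in sex.** At 60% men, two groups of 19 differ by at least 20 percentage points in male share in about 25% of trials. Such a gap moves the expected apnoea prevalence difference by 0.20 × 15.2 = 3.0 points. The standard error of that difference is √(2 × 0.187 × 0.813/19) = 0.127, or 12.7 points.

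**The case against.** The strongest reply is that an unadjusted comparison of randomised groups is valid, and that covariate sets are commonly left to a statistical analysis plan, which is not shown here. The first part stands. The second does not dispose of the point, because the article does not leave the method open: it names one-way ANOVA, which excludes covariates. The logistic regression does not fill the gap, since it is not tied to the group comparison.

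A reader might infer that the plan forgoes the equivalent of 18–54% more patients. That is 1/(1 − R²) − 1 at R² of 15% and 35%. The article supports no R², and the figure leaves out the cost of estimating the covariates.

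A reader might also infer that chance imbalance biases the result. It does not. Under randomisation, that variation is already allowed for in the unadjusted test's error rate, and Step 6 shows that a 20-point sex imbalance shifts the estimate by about a quarter of a standard error (3.0/12.7).

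Two further objections stand and limit the remedy. BMI is not fixed in this trial: Clinical evaluation takes weight before and after a dialysis session, and the hypothesis runs through fluid weight gain between sessions. A BMI taken after randomisation could adjust away part of the effect under study. In addition, the gains above apply to continuous outcomes and do not carry over directly to the binary AHI ≥ 15 behind the sample size.

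**Conclusion.** The point holds as a recommended improvement. The only stated comparison between dialysis groups is unadjusted, and usable covariates are already collected. The plan's test is less precise than it could be if these covariates are prognostic, but it is not invalid.

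The size is conditional. With 57 patients in three equal groups, the net gain runs from about nil (R² = 5%) through 5% (R² = 10%) to 11–45% (R² = 15–35%). The corresponding day-versus-night power at 0.8 SD is 67%, 70% and 72–83%, against 68% unadjusted. These results rest on the assumed R², effect size, allocation ratio and reading of 57 as the total. The document's one relevant figure, the sex difference in apnoea, supports only about 4% by itself. The case therefore rests on a possible gain of 4 to 15 power points against a worst-case loss of about 2.6.

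**What to change.** For continuous outcomes, replace the one-way ANOVA by analysis of covariance on the randomised groups, with sex, age and BMI as pre-specified covariates. State that BMI is the value recorded before randomisation. If AHI is skewed, analyse it on the log or rank scale. Report the adjusted day-minus-night difference with its 95% confidence interval. Naming the covariates now also prevents their being chosen after the data are seen.

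The cost is one sentence in the analysis section and three degrees of freedom, with no new measurement provided that BMI is among the baseline data. Preparing the envelopes in separate series for men and women is optional, and the recommendation does not depend on it.

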OSA is a respiratory disease characterised by the collapse of the upper airways during sleep in predisposed subjects. After chronic obstructive pulmonary disease and asthma, OSA is the most important and widespread respiratory disease, affecting 3% to 7% of the male population and 2% to 5% of the female population between 40 and 65 years of age in the Western world [16]. In Brazil, the prevalence of OSA is even higher at 24.8% in men and 9.6% in women, according to a recent epidemiological study conducted in the city of São Paulo [17].

The causal association between OSA and CKD or whether the 2 diseases result from a common pathophysiologic process has not yet been clarified. Uremic milieu has been implicated as a cause of OSA in patients with CKD. Altered ventilatory drive and chemoreceptors can lead to decreased respiration via a blunted response to ventilatory stimuli, such as hypoxia or acidaemia. Upper airway obstruction can occur from localised oedema or the collapse of the dilator muscles, leading to an increased risk of OSA. Suppression of the respiratory musculature due to metabolic acidaemia/acidosis, osmotic disequilibrium, and a reduction in middle molecule clearance could potentially cause or contribute to OSA [18].

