### Aims and hypotheses

The present study involving patients with CKD was designed with 4 main objectives: (1) to assess the effects of dialysis on sleep parameters and determine the prevalence and severity of sleep disorders; (2) to determine the behaviour of sympathetic and parasympathetic autonomic nervous system activity through an analysis of heart rate variability; (3) to detect upper airway collapsibility as a risk indicator for OSA; and (4) to evaluate levels of depression, anxiety, stress and quality of life. Our hypothesis is that the weather weight gain due to volume overload observed during interdialytic period will influence the degree of collapsibility of the upper airway due to narrowing and predispose to upper airway occlusion during sleep, and to investigate the effects of nocturnal hemodialysis compared to daytime hemodialysis and the influences in the physiological variables of sleep, autonomic nervous system (ANS), and respiratory mechanics and thereby compromise the quality of life in chronic kidney diseases and end-stage renal disease patients undergoing dialysis.

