#### Polysomnography

All the patients will undergo a standard overnight PSG (Embla, A10 version 3.1.2 Flaga, Hs. Medical Devices, Reykjavik, Iceland) at the Sleep Laboratory of Nove de Julho University*.* Polysomnography exams will be held the night before the haemodialysis and approximately 12 hours after this dialysis. All recording sensors will be attached to the patient in a non-invasive manner using tape or elastic bands. The following physiological variables will be monitored simultaneously and continuously: 4 channels for the electroencephalogram (C3-A2, C4-A1, O1-A2, and O2-A1), 2 channels for the electrooculogram (EOG-Left-A2 and EOG-Right-A1), 4 channels for the surface electromyogram (muscles of the submentonian region, anterior tibialis muscle, masseter region, and seventh intercostal space), electrocardiogram (derivation V1 modified), airflow detection via 2 channels through a thermocouple and nasal pressure cannula, respiratory effort of the thorax and abdomen via x-trace belts, snoring and body position sensors, and arterial oxygen saturation and pulse rate via an oximeter.

All the subjects will be monitored by a technician experienced in PSG. Sleep stages will be visually scored in 30-s epochs, and each PSG recording will be analysed manually under blinded conditions by the same examiner with experience in scoring PSG recordings in accordance with international standards established by the Academy of Sleep Medicine Manual for Scoring Sleep and Associated Events. The patients will be instructed to remain as relaxed as possible and sleep naturally, as if at home. All signals will be recorded continuously [34,35].

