**Figure 2 F2:**
[figure not shown]
Schematic representation of the negative expiratory pressure.

Each NEP manoeuvre will be performed each after at least 4 breaths to normalise the breathing pattern. The tests will be performed once with the subject seated comfortably and again in supine position on a cot. In both positions, care will be taken to maintain the comfort of the subjects, with the neck in a neutral position, as it has been documented that the position of the head exerts an influence on upper airway collapsibility [36].

All manoeuvres will be performed with the subjects awake and wearing a nose clip. The airflow and mouth pressure signals will be low-pass filtered and sampled at 200 Hz. Both digital signals will be displayed in real time on the monitor and stored on the computer for subsequent analysis. Signal analysis and solenoid valve control will be performed using software written in 9 LabVIEW 8.2 (National Instruments) developed by the Italian National Research Council, Institute of Biomedicine and Molecular Immunology “A. Monroy.”

NEP application during tidal expiration produces an immediate peak flow followed by a sudden drop of a variable degree. Upper airway collapsibility is to be evaluated by measuring flow limitation as flow drop ($\Delta \dot{V}$) expressed as the percentage of peak flow immediately after NEP administration. To avoid reflex and voluntary reactions to the NEP stimulus, the minimum flow will be identified in the first 200 ms of NEP administration [37].

Upper airway collapsibility will also evaluated by measuring V0.2 immediately after NEP administration. These values will be expressed as the percentage of mean inspiratory volume of the 3 breaths preceding NEP administration. Measured volumes will be accepted only when differences between inspiration and expiration for each of the 3 previous breaths are less than 10%. Values of V_0.2_ and $\Delta \dot{V}$ (%) are calculated as the mean of 4 measurements. Measurements of upper airway collapsibility will be evaluated as expiratory volume in 0.2 s (percentage of the mean inspiratory volume of the 3 breaths preceding NEP application) and as flow drop ($\Delta \dot{V}$), expressed as the percentage of peak flow.

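### The NEP collapsibility measures are correlated with the undivided AHI, although the objective and the test concern upper airway obstruction only

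*Protocol article*

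**What the plan says.** The third objective in Aims and hypotheses is "to detect upper airway collapsibility as a risk indicator for OSA". The Background gives the meaning of the target condition: "OSA is a respiratory disease characterised by the collapse of the upper airways during sleep in predisposed subjects".

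The NEP test section describes a measure of the same trait: "Upper airway collapsibility is to be evaluated by measuring flow limitation as flow drop". V0.2, the volume expired in the first 0.2 s after NEP is applied, is the second measure.

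In Sample size calculation and statistical analysis, V0.2 and flow drop "values will be linearly correlated with the AHI", by Pearson or Spearman according to the distribution. The abbreviation is expanded once, as "apnea/hypopnoea index (AHI" followed by the threshold of 15 used for the sample size, with no restriction by type of event. The same section plans a t test or Mann–Whitney test for "comparisons between individuals with and those without OSA", and ROC curves for V0.2 and flow drop. It gives no rule for who counts as having OSA.

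The Polysomnography section lists "respiratory effort of the thorax and abdomen via x-trace belts" among the recorded signals, together with thermocouple and nasal-pressure airflow, and has one blinded examiner score each recording manually.

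**The concern.** The predictor and the objective are about a collapsing airway. The outcome in the stated correlation is an index of all apnoeas and hypopnoeas. A patient whose events arise without airway collapse raises the AHI, but NEP has no reason to detect that. To the extent that such events occur, they act as noise in the outcome, pull the correlation toward zero and cost power. A weak result could then be read as a failure of NEP when part of the cause is the choice of index.

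The choice is made in the article's own text and is not a detail left open. The recorded effort signals would allow a closer match between test and outcome, but no stated analysis uses them.

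**Working it through.** **Figure in the plan.** The article gives no figure for this correlation. Its only sample size, 57, rests on comparing 16.9% with 50%. At two-sided α = 0.05 and 90% power, the pooled two-proportion formula gives [1.96√(2 × 0.3345 × 0.6655) + 1.282√(0.169 × 0.831 + 0.5 × 0.5)]² / 0.331² = 40.6, so 41 per group or 82 in two groups. The stated 57 is not recovered. That is a separate matter; 57 is used below only as the stated number of patients. The article does not say whether it is a total or per group.

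**Model (assumed).** Write AHI = O + C, with O the obstructive and C the central part. Assume that C is unrelated to NEP and to O, and that C carries a share s of the AHI variance. Then

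corr(NEP, AHI) = r × √(1 − s), where r = corr(NEP, O).

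Power by Fisher's z, two-sided 5%: Φ(atanh(r_obs) × √(n − 3) − 1.96). With n = 57, √54 = 7.348.

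**Assumed r = 0.40:**
- s = 0: r_obs = 0.400; 0.4236 × 7.348 − 1.96 = 1.153; power 87.6%.
- s = 0.20: r_obs = 0.40 × 0.894 = 0.358; 0.3743 × 7.348 − 1.96 = 0.791; power 78.5%.
- s = 0.40: r_obs = 0.40 × 0.775 = 0.310; 0.3203 × 7.348 − 1.96 = 0.394; power 65.3%.
- s = 0.50: r_obs = 0.40 × 0.707 = 0.283; power 57.0%.

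**Other assumed values of r:**

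| True r | s = 0 | s = 0.20 | s = 0.50 |
|---|---|---|---|
| 0.30 | 62.3% | 52.4% | 35.3% |
| 0.50 | 98.1% | 94.3% | 77.5% |

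The shrinkage factor √(1 − s) does not depend on n. Only the power figures do.

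**ROC curve (conditional).** Suppose that OSA status were set by total AHI, that a fraction c of those labelled OSA were central-dominant, and that NEP were uninformative for them. Then AUC = (1 − c)A + 0.5c. For an assumed A = 0.80, this gives 0.77, 0.74 and 0.68 at c = 10%, 20% and 40%. The first condition is not in the article, so this line shows only what would follow if it held.

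**The case against.** Four points on the other side are fair.

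1. A reader might infer that the authors themselves expect central apnoea in CKD, from the Background sentence "Altered ventilatory drive and chemoreceptors can lead to decreased respiration via a blunted response to ventilatory stimuli". The text does not support that. Central apnoea is never named, and the sentence sits in a paragraph on how CKD may cause OSA. Heart failure is listed as a comorbidity and is not an exclusion criterion, but the article nowhere links it to central events. That central events occur at all in this sample is therefore an assumption, though nothing in the eligibility criteria removes such patients.

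2. A reader might also infer that OSA status is AHI ≥ 15, so that central-dominant patients would be mislabelled in the group comparison and the ROC curve. That threshold appears only in the sample-size basis. A diagnosis that uses event type is compatible with the Background definition and with the recorded signals, and the rule may stand in a fuller document that is not shown.

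3. It is tempting to say that total AHI misdirects the answer, or that dialysis changes central and obstructive events differently. Neither is supported. The model above yields attenuation only. Bias away from zero would need central events that are themselves correlated with NEP, for instance because fluid overload drives both, and the article is silent on this.

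4. The magnitudes rest on assumed values of r, s and c.

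All four stand, and they narrow the point to the stated correlation. They do not remove the mismatch there: the sentence fixes an undivided index for an obstruction-specific question.

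**Conclusion.** The point holds for the correlation. V0.2 and flow drop are to be correlated with an AHI that is not limited to obstructive events, while objective 3 and the NEP test concern obstruction alone. Any central events unrelated to collapsibility would attenuate the result.

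The article does not allow the size to be fixed. If the central share of AHI variance lies between 0 and 50% and is independent of NEP and of obstructive events, the correlation is multiplied by a factor between 1 and 0.71. At a true r of 0.40 and 57 patients, power then lies between 88% and 57%. For the with/without-OSA comparison and the ROC curve the point is conditional on an AHI-based definition of OSA. It is an inexpensive improvement to the plan and does not show that the planned result would be wrong.

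**What to change.** In Sample size calculation and statistical analysis, replace the AHI in the V0.2 and flow-drop correlation with an obstructive index from the same polysomnography: obstructive and mixed apnoeas plus hypopnoeas not scored as central, per hour. State how OSA is defined, and use the same index for it in the group comparison and the ROC curve. Report the central apnoea index descriptively, and keep total AHI as a sensitivity analysis.

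The cost is a sentence or two of text and a tabulation of event types by the examiner who already scores every recording; no new measurement is needed. There are two downsides:
- Some hypopnoeas cannot be typed reliably without oesophageal pressure, which is not among the listed signals. Those left untyped would count as obstructive, so some dilution would remain.
- The AHI ≥ 15 prevalences behind the sample size stay on total AHI, so the text should say that the NEP analyses use a different index from the one used to size the trial.

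### The plan names the Student t test for OSA versus non-OSA, so the 5% level is not assured if these uncontrolled groups differ in both size and spread (minor; the Welch t test removes the dependence)

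*Protocol article*

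**What the plan says.** All of this is in the Protocol article, section Sample size calculation and statistical analysis, unless another section is named.

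- **Test.** For OSA against no OSA: "Either the non-paired Student *t* test or Mann–Whitney test will be used for comparisons between individuals with and those without OSA". A Kolmogorov–Smirnov test of normality comes first. No check of spread and no unequal-variance version of the t test is named.
- **Level.** "A 5% level of significance and 95% confidence interval will be applied".
- **Prevalence.** The article gives two rates for an apnoea/hypopnoea index (AHI) of at least 15. One "corresponds to 16.9% of the Brazilian population". For the other, "AHI ≥ 15 had an approximately 50% prevalence rate in patients with CKD undergoing conventional dialysis". The sample size is 57 patients.
- **Groups.** Under Randomization, "participants will be randomized into two intervention group" (daytime and nocturnal haemodialysis), plus a control group not on dialysis. No allocation ratio is stated.
- **Not given.** There is no standard deviation for any outcome by OSA status, no expected number with OSA, and no AHI cut-off that defines OSA for this comparison.

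**The concern.** The Student t test keeps its level when the two groups have the same variance, or nearly so when they have the same size. Here neither condition is under the plan's control. OSA status comes from polysomnography, so the group sizes are known only after the fact. The variables of interest probably include the negative expiratory pressure indices V0.2 and flow drop. These are percentages, for which equal spread in patients with and without OSA cannot be taken for granted.

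If the smaller group is the more variable, the test rejects too often and its confidence interval is too narrow. If the smaller group is the less variable, the test rejects too rarely and the interval is too wide. A normality test detects neither. The comparison bears on the third objective in the Aims and hypotheses section, upper airway collapsibility as a risk indicator for OSA.

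**Working it through.** **1. The plan's own figure.** With 16.9% v 50%, two-sided α = 0.05, 90% power and equal groups:

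n per group = [1.960·√(2·0.3345·0.6655) + 1.2816·√(0.169·0.831 + 0.5·0.5)]² / (0.331)² = (1.308 + 0.801)² / 0.1096 ≈ 40.6, so 41 per group and 82 in total.

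A one-sided test needs 33 per group, 66 in total. Among the variants tried, a total of 57 appears only with one-sided α, 80% power and 2:1 allocation (38 + 19). That discrepancy is a separate matter and does not bear on this point. Below, 57 is taken as the total.

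**2. Possible OSA splits among 57.**

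- 50% throughout: 57 × 0.5 = 28.5, so about 28 v 29. Chance alone gives a 95% binomial range of 21 to 36 with OSA.
- 50% in 38 dialysed patients and 16.9% in 19 controls (1:1:1 allocation assumed): 19 + 3.2 = 22.2, so about 22 v 35.
- 16.9% throughout: 57 × 0.169 = 9.6, so about 10 v 47. This is an extreme bound only.

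**3. Why pooling matters.** Let the SD be s in the OSA group (size n₁) and 1 in the other (size n₂).

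- True variance of the mean difference: s²/n₁ + 1/n₂.
- Average variance that the pooled test uses: [(n₁−1)s² + (n₂−1)]/55 × (1/n₁ + 1/n₂).

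| Split | s | True variance | Variance used | Ratio |
|---|---|---|---|---|
| 22 v 35 | 2 | 4/22 + 1/35 = 0.2104 | (118/55) × 0.0740 = 0.1588 | 1.32 |
| 22 v 35 | 0.5 | 0.25/22 + 1/35 = 0.0399 | (39.25/55) × 0.0740 = 0.0528 | 0.76 |
| 28 v 29 | 2 | 4/28 + 1/29 = 0.1773 | (136/55) × 0.0702 = 0.1736 | 1.02 |

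At 22 v 35 the pooled test understates the variance of the difference in the first row and overstates it in the second. At 28 v 29 the two nearly agree.

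**4. Type I error by simulation** (normal data, equal means, nominal 5%, 100,000 runs per setting). SD ratio is OSA/non-OSA.

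| Split | SD ratio 0.5 | 0.667 | 1 | 1.5 | 2 | Welch, all ratios |
|---|---|---|---|---|---|---|
| 28 v 29 | 5.0% | 5.0% | 5.0% | 5.3% | 5.5% | 5.0–5.1% |
| 22 v 35 | 2.6% | 3.3% | 4.9% | 7.4% | 9.0% | about 5.0% |
| 10 v 47 | 0.4% | 1.2% | 5.1% | 12.9% | 19.8% | 5.0–5.2% |

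At 22 v 35 with SD ratio 2, the pooled 95% interval therefore covers about 100 − 9.0 = 91%. With SD ratio 0.5 it covers about 97.4%. The plan's alternative, Mann–Whitney, gives 3.9% to 7.5% at 22 v 35 over the same ratios (20,000 runs). It softens the problem without removing it.

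**5. Power if variances are equal** (difference of 0.8 SD, 40,000 runs). At 22 v 35: Student 82.5%, Welch 82.2%. At 10 v 47: 61.9% and 57.0%.

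**The case against.** The strongest reply is that nothing in the article shows the problem will occur. Its only figure for dialysed patients is about 50%, which gives 28 v 29, and there the level is kept. The 22 v 35 split needs an allocation ratio that the article does not state and a general-population rate applied to controls with kidney disease. No standard deviation is given, so neither unequal spread nor its direction is established. Logistic regression and ROC curves are also planned for related questions and do not assume equal variances. Finally, the form of a t test is a detail that a condensed article may leave to the analysis plan.

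Most of this stands, and it limits the point to a conditional one. Two things remain. The article does not leave the test open: it names the Student t test, which in ordinary usage is the pooled test. And a split near 22 v 35 does not need the control-group assumption, because it lies inside the chance range of 21 to 36 even at 50% prevalence.

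A reader might infer three stronger claims that the documents do not support:

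- **That the OSA groups will be unequal and the 5% level will fail.** Neither the group sizes nor the spreads are known.
- **That error near 20% is to be expected.** That figure needs 10 v 47, which applies the general-population rate to every patient although two of the three planned groups are on haemodialysis.
- **That the shift comparison by one-way analysis of variance has the same defect.** Those groups are described as randomised, so the argument from observed status does not apply. With 19 per group the simulated error is 5.0% to 6.3% for SDs differing up to twofold. Larger errors (3.3% to 11.8%) appeared only with an assumed 25/20/12 split, which nothing in the article indicates.

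**Conclusion.** The point holds as a minor, conditional one, for the OSA comparison only. The named test is valid if the groups are nearly equal in size or in spread. The plan controls neither and checks neither. Under the stated assumptions for 22 v 35, the real level lies between about 2.5% and 9% for SD ratios of 0.5 to 2, liberal or conservative according to which group varies more. At 28 v 29 it stays between 5.0% and 5.5%. The SD ratios, the 1:1:1 allocation and the 16.9% rate in controls are assumptions, not facts from the article.

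**What to change.** In the section Sample size calculation and statistical analysis, replace the non-paired Student t test for OSA versus non-OSA by the Welch t test, and report the matching unequal-variance 95% confidence interval. Apply it as the default, without a preliminary test of variances. No change to the analysis of variance is asked for on this ground.

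The change is one phrase, needs no further patients or data, and is available in standard software. If variances are in fact equal, it costs about 0.3 points of power at 22 v 35 (82.5% to 82.2%) and about 5 points at 10 v 47 (61.9% to 57.0%). It does not alter the Mann–Whitney branch, where a smaller sensitivity to unequal spread remains.
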